#### Conclusion about the sample size

Thus, considering the two methods, a sample size of around 698 patients is suggested of this study.

#### DATA COLLECT

Data collection will perform through an electronic document in the electronic system at the study hospital, specially prepared to collect and record research data. This document will present the following information about patient: general data (age, weight, comorbidities), clinical history, physical examination (heart rate, respiratory rate, temperature, blood pressure, cardiac, pulmonary and abdominal auscultation, otoscopy and oroscopy), diagnosis, diagnostic hypothesis and management.

The data collection instrument will be the same for the consultation with Tytocare and the traditional consultation. However, PEDIATRICIAN 2 will not have access to the PEDIATRICIAN 1 results registration form and vice versa, to ensure data confidentiality and research suitability.

A study coordinator will be able to access the two records, in order to see if there is a discrepancy between the diagnoses or diagnostic hypotheses. When this occurs, the coordinator will inform PEDIATRICIAN 2 if he wants to discuss the case with PEDIATRICIAN 1 and the pediatric resident who treated the patient with Tytocare®.

#### ANALYSIS OF RESULTS

The results of physical examinations (Tytocare® vs traditional) and diagnostic hypotheses will be analyzed by comparing paired proportions and agreement between methods.

After meeting the expected sample, we will analyze whether the statistical tests will demonstrate the hypothesis of the study, that the physical examination obtained by Tytocare or diagnosis supported by the device is equivalent to the traditional physical examination, in the parameters of clinical signs and diagnostic hypothesis, as well as that Tytocare can be delivered to a telemedicine service.

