## FLOWCHART OF THIS STUDY

The single-arm, non-randomized clinical trial in second step will consist of selecting patients classified as code green (low risk), who will undergo two medical consultations and two physical examinations (Tytocare® and traditional), with the aim of comparing the results between these two modalities of examination and diagnosis. The flowchart will be as detailed in the steps below and illustrated in figure 1.

[figure not shown]

Figure 1. Flowchart of patient consultations in the study.

**Step 1:** The patient, after going through the nursing screening and being classified as code green and accepting to participate in the study, will be submitted to the first consultation with Tytocare® intervention, in the room 1. This consultation will be performed by a pediatric resident of the first year, whose inexperience should mimic that of the non-specialist doctor in the health units. The resident will collect information related to past medical history, current symptoms, and will perform a physical examination using Tytocare®. This device allows obtaining the following finding: heart rate, respiratory rate, body temperature, cardiac, pulmonary and abdominal

auscultation, otoscopy and oroscopy. In this room, Tytocare® and an attached computer will be available for data recording by the Pediatrics Resident.

**Step 2:** As the data is entered into the computer, it will be transmitted from the Tytocare® platform to the electronic system, and a second physician, called PEDIATRICIAN 1, will receive the results and images of the physical examination obtained by Tytocare®. PEDIATRICIAN 1 will be allocated in a room, called the situation room, guiding the resident and confirming the patient's care, thus configuring a second opinion on the case, thus characterizing the teleinterconsultation. These two doctors will decide together at a diagnostic hypothesis, diagnosis and/or course to be taken, which will be recorded in the data collection form (electronic document in the electronic system).

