**Step 3:** The patient will be invited to go to the second consultation, which we will call a traditional consultation, and will be performed by another pediatrician, called PEDIATRICIAN 2. In this consultation, the doctor will perform the entire routine procedure (anamnesis with physical examination), without the use of Tytocare®. The traditional physical examination consists of obtaining the same clinical parameters using usual means or equipment such as a digital thermometer, sphygmomanometer, stethoscope and otoscope. This second consultation will take place in the hospital's emergency medical office, according to the service's demand flow. This physician will record your finding (vital signs, diagnostic hypothesis and conducts) on a patient registration form in the electronic system. In this moment, PEDIATRICIAN 2 will not have access to information registered for PEDIATRICIAN 1, in order to not compromise the results.

**Step 4:** The PEDIATRICIAN 2 will decide and communicate the diagnosis to the parents. Your conduct and/or diagnosis and treatment proposal will perform.

If there is a divergence between diagnoses, this will be observed in real time by the study coordinator and, in order to ensure patient safety, PEDIATRICIAN 2 can consult and discuss with the resident and PEDIATRICIAN 1. Furthermore, the PEDIATRICIAN 1 can use the results and images from the Tytocare® physical examination, however, without being able to make changes to the information in the data collection document.

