## SAMPLE SIZE AND STATISTICAL ANALYSIS

When comparing physical examinations by the two methods (captured by telemedicine and traditional physical examination), two statistical elements are involved, the comparison of paired proportions and the agreement between methods.

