### Comparison of paired proportions

This type of comparison is usually done using the McNemmar test, as it considers the pairing of samples when comparing proportions. The sample calculation is then given considering that records from group A are paired with records from group B, this occurs in cases where two methods evaluate the same samples. McNemmar's test also considers that one wants to verify the equality of probability of a finding.

The sample size calculation requires some parameters. For our calculation, we consider four parameters. We will use the alpha of 0.05 and the statistical power (Bheta) of 0.80.

The expected total proportions of change from positive to negative and from negative to positive are also considered. For the calculation of the order of these two proportions it does not matter.

We see in the following table a combination of proportions that result in different sample sizes.

| Prop 1\Prop 2 | 0.10 | 0.15 | 0.20 | 0.25 |
|----------------------|-------------|-------------|-------------|-------------|
| 0.05          | 468  | 155         | 85          | 57          |
| 0.10          |             | 781         | 233         | 120         |
| 0.15          |             |             | 1095        | 311         |
| 0.20          |             |             |             | 1408        |

If these two proportions were too large, it would indicate that the methods are not comparable, therefore, and also for the practical aspect of the study, a sample size of 468 was chosen for the aspect of comparing paired proportions.

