### Concordance between methods

Verification of concordance between methods will be performed using the kappa statistical method. Again we have a combination of parameters in the calculation to establish the sample size.

Bujang's proposal (2017) uses the quantities of categories, power and alpha for the sample calculation. Assuming 80% power with an alpha of 0.05 and knowing that we have two possible categories in each response (found or not found), we have the following combination of suggested sample sizes for each combination of proportions.

| Prop 1 \ Prop 2 | 0.0 | 0.3 | 0.5 | 0.7 |
|------------------------|------------|------------|------------|------------|
| 0.2             | 194        |            |            |            |
| 0.3             | 85         |            |            |            |
| 0.4             | 47         | 698 |            |            |
| 0.5             | 29         | 169        |            |            |
| 0.6             | 20         | 72         | 563 |            |
| 0.7             | 14         | 39         | 133        |            |
| 0.8             | 10         | 23         | 54         | 363        |
| 0.9             | 7          | 14         | 27         | 79         |

Considering a statistical power of 90%, we have the following suggestion of sample sizes.

| Prop 1 \ Prop 2 | 0.0 | 0.3 | 0.5 | 0.7 |
|------------------------|------------|------------|------------|------------|
| 0.2             | 259        |            |            |            |
| 0.3             | 113        |            |            |            |
| 0.4             | 62         | 927 |            |            |
| 0.5             | 38         | 222        |            |            |
| 0.6             | 25         | 94         | 742 |            |
| 0.7             | 17         | 49         | 171        |            |
| 0.8             | 12         | 28         | 68         | 471        |
| 0.9             | 8          | 17         | 32         | 96         |

With this information, this method suggests a sample size of 698 patients (according to the proportions of the study, using the 80% power table and considering 0.3 and 0.4 proportions).

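### Heart rate, respiratory rate and temperature are numeric, but the plan names only McNemar and kappa and gives no cut-off, so equivalence of these readings cannot be shown

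*Combined protocol and SAP*

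**What the plan says.** - **Parameters.** Step 1 of the study flowchart lists what the device obtains: "heart rate, respiratory rate, body temperature, cardiac, pulmonary and abdominal" auscultation, then otoscopy and oroscopy. For the comparator, Step 3 says: "The traditional physical examination consists of obtaining the same clinical parameters using usual means or equipment".
- **Common form.** Under DATA COLLECT, one instrument serves both consultations and records "physical examination (heart rate, respiratory rate, temperature, blood pressure, cardiac, pulmonary and abdominal auscultation, otoscopy and oroscopy), diagnosis, diagnostic hypothesis and management". Blood pressure is on this form but not in the device list.
- **Methods.** The statistical section says that "two statistical elements are involved, the comparison of paired proportions and the agreement between methods". On the first element it says: "This type of comparison is usually done using the McNemmar test, as it considers the pairing of samples when comparing proportions". On the second: "Verification of concordance between methods will be performed using the kappa statistical method".
- **Data type.** The kappa sample size is calculated "knowing that we have two possible categories in each response (found or not found").
- **Scope.** ANALYSIS OF RESULTS applies these two elements to everything: "The results of physical examinations (Tytocare® vs traditional) and diagnostic hypotheses will be analyzed by comparing paired proportions and agreement between methods". The same section aims to show equivalence in clinical signs and diagnostic hypothesis.

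The documents give no cut-off for any vital sign, no coding or matching rule for diagnoses, no method for numeric agreement and no acceptable difference.

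**The concern.** Three of the eight device parameters are measurements. McNemar and two-category kappa can be applied to them only after each reading is split at a cut-off. That discards the size of the disagreement and makes the answer depend on the cut-off, in a population aged 0 to 18 in which normal heart and respiratory rates change with age. Because no cut-off is fixed, it could be chosen after the data are seen.

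McNemar asks only whether two proportions are equal. If the methods scatter randomly around each other, equal numbers of children cross the cut-off in each direction and the test sees nothing, however wide the scatter. At stake is whether the trial can support its own equivalence hypothesis for the numeric signs. For diagnosis the problem is smaller: without a coding rule, what counts as agreement is undefined.

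**Working it through.** **1. The plan's own figures.** These reproduce, which confirms what they were built for.

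- McNemar, two-sided α = 0.05, power 0.80, discordant proportions 0.05 and 0.10: n = [1.96·√(p₁+p₂) + 0.842·√(p₁+p₂−(p₁−p₂)²)]² / (p₁−p₂)² = [1.96·√0.15 + 0.842·√0.1475]² / 0.0025 ≈ 468.6. The plan states 468.
- Kappa, 0.3 against 0.4 (the plan labels these proportions), two categories with 50/50 marginals: n = [1.96·√(1−0.3²) + 0.842·√(1−0.4²)]² / 0.1² ≈ 697.5, rounded up to 698. The plan states 698.

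There is no arithmetic error. The trial size rests on a two-category response.

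**2. Random scatter (heart rate).** Assumptions, none from the documents: SD between children 20 bpm, independent error SD 10 bpm in each method, no bias, cut at the 90th percentile, 698 pairs.

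- SD of the paired difference = √(10² + 10²) = 14.1 bpm, so the 95% limits are ±1.96 × 14.1 ≈ ±28 bpm.
- By simulation, McNemar rejects in about 5% of trials, which is just its type I error rate.
- Kappa is about 0.5. With error SD 2 bpm instead (limits about ±5.5 bpm), kappa is 0.89. So kappa responds to scatter and McNemar does not.

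**3. Dependence of kappa on the cut-off.** In standardised units (true-value SD 1, SD of differences 0.5, limits ±0.98), kappa is 0.70, 0.67 and 0.60 when 50%, 20% and 5% of readings lie above the cut-off. The readings agree equally well in all three cases.

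**4. Small bias (temperature).** Assumptions: mean 36.8 °C, SD 0.6 between children, error SD 0.2 per method, device bias 0.1 °C, 698 pairs, McNemar without continuity correction.

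| Cut-off (°C) | Trials with significant McNemar |
|---|---|
| 37.3 | about 97% |
| 37.5 | about 92% |
| 37.8 | about 71% |
| 38.0 | about 49% |
| 38.5 | about 9% |

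The bias is the same in every row; only the cut-off differs. With a continuity correction the figure at 37.8 °C is about 63%.

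**5. What 698 pairs would give on the numeric scale.** In units of the SD of the paired differences, which the documents do not give:

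- 95% CI half-width for the bias = 1.96/√698 = 0.074 SD.
- 95% CI half-width for each limit of agreement ≈ 1.96·√(3/698) = 0.13 SD.

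In the heart-rate scenario these are 0.074 × 14.1 ≈ 1.0 bpm and 0.128 × 14.1 ≈ 1.8 bpm. Precision is ample without more patients.

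**The case against.** The results section does not itself name McNemar, kappa or two categories, and the two-category statement is an input to a sample-size calculation. Nowhere do the documents say that vital signs will be dichotomised. That is correct, so the point is that no usable method is specified for the numeric readings, not that a wrong one has been expressly chosen. No other method is named, so the gap remains.

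Three stronger readings are tempting, and the documents do not support them.

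- A reader might infer that a badly scattered device would pass. The plan pairs McNemar with kappa, kappa falls as scatter grows, and no pass rule is stated. The ±28 bpm also includes the assumed error of the traditional method, so it is not the device's scatter alone.
- A reader might infer that the diagnosis hypothesis cannot be tested at all. Each diagnosis could be scored found or not found in each consultation, which makes both statistics computable, and kappa extends to several nominal categories. What is missing is the coding rule. That diagnosis has many categories is itself inferred from its nature.
- A reader might infer that blood pressure is to be compared without a device value. It is on a shared form, and no section expressly makes it a device comparison. This needs clarifying only.

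A further objection stands against a simple remedy. The examinations are separate consultations, the second follows the flow of demand in the service, and green-code patients have an average time of care within four hours. Heart rate and temperature can truly change in between, so limits of agreement would mix real change with measurement error. The two-category methods also suit the other five device parameters: three auscultations, otoscopy and oroscopy.

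**Conclusion.** The concern holds for the three numeric vital signs. The named methods need a cut-off that the plan does not give, their results depend on it, and neither expresses the difference in the units of measurement. Equivalence of these readings therefore cannot be shown as planned. For diagnosis, the finding is limited to the missing coding rule.

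The percentages illustrate the mechanism. They rest on assumed means, SDs, error sizes and cut-offs and do not predict this trial's results. That McNemar is insensitive to symmetric scatter, and that both statistics depend on the cut-off, does not rest on the particular values chosen. The sample size of 698 is not in dispute on this point.

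**What to change.** - **Heart rate, respiratory rate, temperature.** Make the primary analysis the Bland-Altman bias and 95% limits of agreement, each with a CI. Judge them against acceptable limits fixed before any comparative data are examined. Check whether the differences depend on age or on the size of the reading. Store the actual readings from both methods.
- **Interval between examinations.** Record it for each child and account for it, for example by a sensitivity analysis restricted to short intervals, because the limits also contain true change.
- **Diagnosis.** Code both records, blind to method, into a fixed list. Report multi-category kappa and percent agreement with CIs.
- **Auscultation, otoscopy, oroscopy.** Keep McNemar and two-category kappa.
- **Blood pressure.** State that it is outside the device comparison, or reconcile the device list in the flowchart section with the form under DATA COLLECT.

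The cost is a revision of the analysis text, a time stamp for each examination if none is kept, blinded coding of diagnoses and a little more analysis. The main effort is agreeing the acceptable limits in advance. No extra patients or visits are needed.

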## **METHODOLOGY**

This study is a prospective, single-arm, non-randomized clinical trial to compare a mobile physical device linked to telemedicine with traditional physical examination in the care of patients in the emergency department of a pediatric hospital.

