## PARTICIPANTS

Eligible participants in this study will be those classified as low risk (classified as green) in the triage performed by nurses in the emergency room.

Both hospitals have a risk classification protocol to stratify and classify all patients who arrive at the Emergency room. This classification is performed by the nurse and the protocol consists of five color codes (red, orange, yellow, blue and green):

- Red: serious patient, considered as an emergency, with immediate care;
- Orange: patient considered urgent, with care within a maximum period of 15 minutes;
- Yellow: patients who do not present conditions that characterize medical urgency, however, are identified as patients who require particular conditions for prioritization. As those who have comorbidities, associated with clinical conditions with potential risk for complications, with a goal of care of up to one hour;
- Green: patients who do not present clinical conditions that characterize medical urgency, with an average time of care within four hours;
- Blue: patients who have specific needs for procedures. These patients will not be classified because they do not have clinical circumstances, but they will be prioritized over those classified as non-urgent (Green), such as: tube replacement, administration of medication or dressings. Your average handle time target is two hours.

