### Exclusion criteria:

- Patients classified in red, orange, yellow and blue codes;

- Patients in which the legal guardian or one of the parents does not consent to participation;
- Patient who does not agree to sign the Term of Assent/consent.

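### The equivalence hypothesis does not name the green-triaged population enrolled, and McNemar's test and kappa alone will not show how well the device recognises abnormal findings

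*Combined protocol and SAP*

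**What the plan says.** The PARTICIPANTS section restricts eligibility to "those classified as low risk (classified as green) in the triage performed by nurses" and describes that code as "patients who do not present clinical conditions that characterize medical urgency, with an average time of care within four hours". The exclusion criteria remove "Patients classified in red, orange, yellow and blue codes". The study flowchart section repeats the restriction: the second step consists of "selecting patients classified as code green (low risk), who will undergo two medical consultations and two physical examinations".

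Two other places describe the question without it. METHODOLOGY sets the comparison "in the care of patients in the emergency department of a pediatric hospital". ANALYSIS OF RESULTS says the tests are to demonstrate "that the physical examination obtained by Tytocare or diagnosis supported by the device is equivalent to the traditional physical examination". That sentence goes on to limit the claim to clinical signs and diagnostic hypothesis, and adds that the device can be used in a telemedicine service. It does not say in which patients.

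The planned analyses are McNemar's test for paired proportions and kappa for agreement, each finding being recorded as found or not found. The plan states no prevalence for any finding, no minimum number of positives, no measure of agreement among positives, and no acceptance threshold or equivalence margin.

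**The concern.** There are two linked gaps.

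The first is the population. The trial will hold no red, orange, yellow or blue patients. Yellow includes children who are not urgent but are prioritised, described as "As those who have comorbidities, associated with clinical conditions with potential risk for complications". A favourable result can speak only for the green stream, and the sentence that the tests are meant to demonstrate does not say so.

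The second is the measure. For a clinical sign, the main question about a remote examination is how often it picks up what the traditional examination picks up. McNemar's test compares the two marginal proportions, so misses and false positives can cancel. Kappa mixes agreement on positives and on negatives and depends on prevalence. If a finding is uncommon in the green stream, a device that recognises it poorly could give results that nothing in the plan would flag.

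**Working it through.** **1. The plan's own figures.** Both sample sizes reproduce with two-sided alpha 0.05 and 80% power.

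- McNemar, discordant proportions 0.05 and 0.10: n = [1.960·√0.15 + 0.842·√(0.15 − 0.05²)]² / 0.05² = 468.6 (plan: 468).
- Kappa 0.3 against 0.4: n = [1.960·√V(0.3) + 0.842·√V(0.4)]² / 0.1², where V(k) = (1−k)·[(1−k)(1−2k) + k(2−k)/(2π(1−π))] and π is the prevalence. At π = 0.5, V(0.3) = 0.91 and V(0.4) = 0.84, so n = 697.5 (plan: 698).

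The second figure therefore holds for a finding present in half the children, a condition the plan does not state. For the same contrast, 698 children give power of 74%, 64%, 43%, 27% and 14% at prevalences of 30%, 20%, 10%, 5% and 2%.

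**2. Number of positives.** Positives = 698 × prevalence. Every prevalence here is an assumption. The intervals are exact (Clopper-Pearson) and assume that the device agrees on about 86% of positives.

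| Assumed prevalence | Positives | Agreeing | Exact 95% interval for positive agreement |
|---|---|---|---|
| 1% | 7 | 6 | 42-100% |
| 2% | 14 | 12 | 57-98% |
| 5% | 35 | 30 | 70-95% |
| 10% | 70 | 60 | 75-93% |
| 20% | 140 | 120 | 79-91% |
| 50% | 349 | 300 | 82-89% |

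**3. Misses balanced by false positives.** Take prevalence 2%, half the positives missed, and as many false positives. The cell proportions are 0.01 (both positive), 0.01 and 0.01 (discordant), and 0.97 (both negative).

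- McNemar: the discordant proportions are equal, so the null is exactly true.
- Kappa: observed agreement is 0.98 and chance agreement is 0.02² + 0.98² = 0.9608. Kappa = (0.98 − 0.9608)/(1 − 0.9608) = 0.49, above both planning values of 0.3 and 0.4.

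**4. What kappa leaves open.** With equal margins, positive agreement = π + kappa·(1 − π). A kappa of 0.49 means positive agreement of 0.02 + 0.49 × 0.98 = 50% at 2% prevalence, but 0.5 + 0.49 × 0.5 = 74.5% at 50% prevalence. The same kappa can describe quite different recognition of a finding.

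**5. Misses without false positives.** Take prevalence 1% with half missed. Discordant pairs are expected in 698 × 0.005 = 3.49 children, all in one direction. Exact McNemar gives p = 2 × 0.5⁵ = 0.063 with five such pairs and 2 × 0.5⁶ = 0.031 with six, so at least six are needed. The chance of six or more from a binomial (698, 0.005) is 14%. Kappa in this case is 0.66.

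**The case against.** The green restriction is not hidden. The participants section, the eligibility criteria and the flowchart section all state it, and the flowchart section ties the comparison to those children. Read as a whole, the protocol may intend its hypothesis for them alone. This stands as a reason to treat the missing label as a matter of wording. It does not remove the need for the label in the sentence that the tests are to demonstrate.

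A reader might infer several stronger points that the documents do not support:

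- *That equivalence is claimed without any limit, or will be applied to other triage codes.* The hypothesis does limit the parameters, and nowhere is application to other codes announced. METHODOLOGY may simply describe the setting. The remark about the resident, "whose inexperience should mimic that of the non-specialist doctor in the health units", concerns the examiner's experience and says nothing about which patients health units see.
- *That the trial will hardly contain abnormal findings.* Green is defined by absence of urgency, not absence of signs, and children coded green may well have abnormal ears, throats or chests. The plan's inputs point to common findings: the McNemar case requires one method to be positive in at least 10% of children, and the kappa figure corresponds to 50%.
- *That children with comorbidities are absent.* Comorbidity is not an exclusion criterion and is recorded for every child. Only those coded yellow are removed.
- *That a device missing every positive could pass.* At 2% prevalence with no false positives, overall agreement would be 98%, but that is not a planned measure. Kappa would be 0, and McNemar with 14 pairs against 0 gives p = 2 × 0.5¹⁴ = 0.0001. The weakness concerns partial misses of uncommon findings.

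It is also fair to say that kappa is not blind in the 2% example, since 0.49 does register disagreement. But the plan has no threshold against which to judge that value, and its planning values are lower.

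**Conclusion.** The concern holds in a limited form. It is certain from the text that the hypothesis omits the enrolled population. It follows from the arithmetic that McNemar's test and kappa, used without an acceptance threshold, do not establish how well the device recognises abnormal findings.

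The size depends on prevalences that the plan does not give. At 20% or more there are at least 140 positives, and positive agreement would be estimated to within several percentage points. At 1-2% there are 7 to 14, and the interval is too wide to say much. The 14% detection rate and the kappa of 0.49 are illustrations at assumed prevalences and error patterns, not predictions. Enrolling only green patients is a legitimate choice, and the sample-size arithmetic is correct for its inputs. What needs changing is the stated claim and the reporting that supports it.

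**What to change.** 1. In ANALYSIS OF RESULTS, and correspondingly in METHODOLOGY, state the hypothesis and conclusion for children aged 0-18 triaged green at the two hospitals. Say that no equivalence is claimed for other triage codes.
2. For each binary finding, report the number positive by the traditional examination, and the positive and negative agreement of the device with exact 95% intervals, alongside kappa and McNemar's test.
3. State equivalence for a finding only if the lower 95% limit of positive agreement reaches a minimum that the sponsor fixes before analysis. Otherwise report that finding as inconclusive.

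The cost is revised wording, one pre-specified threshold and one table built from data already collected. Enrolment and data collection do not change. The downside is a narrower claim, with some rare findings declared inconclusive.

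### The plan sets out to demonstrate equivalence, but McNemar's test of difference cannot show it and the kappa analysis has no success criterion

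*Combined protocol and SAP*

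**What the plan says.** ANALYSIS OF RESULTS gives the hypothesis that the statistical tests are meant to demonstrate: "the physical examination obtained by Tytocare or diagnosis supported by the device is equivalent to the traditional physical examination". Examination results and diagnostic hypotheses "will be analyzed by comparing paired proportions and agreement between methods".

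For the first of these analyses, the section Comparison of paired proportions says "This type of comparison is usually done using the McNemmar test" and describes its purpose as follows: "McNemmar's test also considers that one wants to verify the equality of probability of a finding". The sizing inputs are "We will use the alpha of 0.05 and the statistical power (Bheta) of 0.80", and from the table cell for discordant proportions 0.05 and 0.10, "a sample size of 468 was chosen for the aspect of comparing paired proportions". The only remark on how much disagreement is acceptable is "If these two proportions were too large, it would indicate that the methods are not comparable", with no limit attached.

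For the second analysis, Concordance between methods says "Verification of concordance between methods will be performed using the kappa statistical method". The final sample size of about 698 comes from its 80% power table at 0.3 against 0.4. The document calls these values proportions, but the calculation reproduces when they are read as kappa values.

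The document gives no equivalence margin, no confidence-interval rule, no minimum kappa and no rule for combining the two analyses.

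**The concern.** McNemar's null hypothesis is that the two methods yield the finding equally often. Rejecting it shows a difference. Failing to reject it shows only that the data did not reveal one, and that becomes more likely as evaluable pairs become fewer. The test also looks only at the imbalance between the two kinds of discordant pair. If the device misses a finding in as many children as it wrongly reports one, McNemar sees no problem, however many children are involved.

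Kappa covers that second weakness because it falls as discordance rises. But a kappa estimate supports equivalence only against a stated minimum, and none is stated. What is at stake is the study's main claim. As written, no pre-specified result would confirm or refute it, so the standard could be settled after the data are seen.

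**Working it through.** **Inputs.** From the document: alpha 0.05, power 0.80, discordant proportions 0.05 and 0.10, sample sizes 468 and 698, kappa 0.3 against 0.4. Assumed: two-sided alpha (not stated, but it reproduces the table), 50% prevalence for kappa, and the equivalence margins.

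**1. Reproducing the plan's figures.** Let ψ be the sum of the two discordant proportions and d their difference.

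- McNemar: n = [1.96√ψ + 0.842√(ψ − d²)]² / d². With ψ = 0.15 and d = 0.05, n = 468.6, against 468 stated. A one-sided alpha would give 369. The other nine table cells also reproduce closely.
- Kappa: at 50% prevalence with equal marginals, kappa = 2 × raw agreement − 1, and its large-sample variance is (1 − κ²)/n. So n = [1.96√(1 − 0.3²) + 0.842√(1 − 0.4²)]² / 0.1² = 697.5, against 698 stated.

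Both sizes are therefore correct for what they test: detecting a difference, and showing kappa above 0.3 when it is truly 0.4.

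**2. How often McNemar is non-significant at 698.** Power = Φ[(d√n − 1.96√ψ) / √(ψ − d²)].

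| Discordant proportions | True difference | Non-significant |
|---|---|---|
| 5% / 10% | 5 points | 1 − 0.928 = 7% |
| 6% / 9% | 3 points | 1 − 0.535 = 47% |
| 20% / 25% | 5 points | about 50% |
| 20% / 20% | 0 | about 95% |
| 25% / 25% | 0 | about 95% |

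For the symmetric rows the 95% follows from the test's own 5% level, and simulation with 100,000 runs agrees. At 50% prevalence, 20%/20% is raw agreement of 0.60 and kappa 2 × 0.60 − 1 = 0.20. For 25%/25%, kappa is 0.

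**3. What kappa adds.** At true kappa 0.20 and n = 698, the standard error is √(0.96/698) = 0.037, so 95% of estimates fall between about 0.13 and 0.27. Kappa would expose that disagreement. However, the sizing alternative of 0.4 is itself raw agreement of 0.4 × 0.5 + 0.5 = 0.70, which leaves 30% of children with contradictory findings. Rejecting kappa = 0.3 would not amount to equivalence.

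**4. What 698 pairs give under a margin rule.** For two one-sided 5% tests with margin m and true difference d, SE = √[(ψ − d²)/698], and power = Φ[(m − d)/SE − 1.645] + Φ[(m + d)/SE − 1.645] − 1. For example, with ψ = 0.15, d = 0 and m = 0.05, SE = 0.01466 and power = 2Φ(1.766) − 1 = 0.92.

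| Margin (assumed) | Total discordance | True difference | Power |
|---|---|---|---|
| ±5 points | 15% | 0 | 92% |
| ±5 points | 15% | 1 point | 85% |
| ±5 points | 15% | 2 points | 66% |
| ±5 points | 15% | 3 points | 39% |
| ±5 points | 20% | 0 | 81% |
| ±5 points | 40% | 0 | 34% |
| ±3 points | 15% | 0 | 31% |

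At the plan's own 5%/10% split the true difference sits on a 5-point margin, and the rule passes 5% of the time, as it should. For 80% power at 15% discordance and zero true difference, n = ψ(1.645 + 1.282)²/m² gives 514 pairs at ±5 points and 1,428 at ±3.

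**The case against.** The strongest reply is that McNemar does not stand alone. The plan names two analyses, applies both, and takes its final sample size from kappa. The 20%/20% example has kappa 0.20, below the plan's lower sizing value of 0.3, so the planned agreement analysis would reveal it. The plan also recognises that large discordant proportions would count against the device. All of this stands. A reader might infer that heavy disagreement would go unnoticed, and the document does not support that.

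A reader might also infer that the plan will declare equivalence whenever McNemar's p exceeds 0.05. No section says so, and the percentages in the McNemar table are conditional on that reading. It is still the only McNemar result that could count in favour of the hypothesis, given that the test is described as verifying equality.

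Two further inferences do not hold. The 5-point contrast is a difference chosen for detection, partly on practical grounds, and is not a margin the plan has adopted. Nor can it be said without qualification that 698 patients suffice: the 92% needs a true difference of exactly zero and every pair evaluable.

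What the reply does not supply is a criterion. Kappa has no minimum, McNemar has no margin, and nothing says how the two combine.

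**Conclusion.** The concern holds in this form: equivalence is claimed without a margin, a minimum kappa or a decision rule; McNemar's test cannot establish it; and kappa, which responds to the disagreement McNemar misses, is planned without a criterion. This goes to the study's stated hypothesis and should be put right before the data are analysed.

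On the conditional reading that non-significance counts as support, the size at 698 patients is a 7% miss rate for 5% against 10% discordant, 47% for 6% against 9%, and about 95% non-significance under 20%/20%. The McNemar figures assume two-sided alpha and 698 evaluable pairs. The kappa figures assume 50% prevalence. The sample-size arithmetic itself is not in error.

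**What to change.** For each examination finding and for the diagnostic hypothesis, replace the present wording with a two-part rule. Conclude equivalence only if:

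1. the 90% confidence interval for the paired difference in proportions (a paired score interval such as Tango's, equivalent to two one-sided 5% tests) lies wholly within a margin that the investigators pre-specify and justify; and
2. the lower confidence bound for kappa exceeds a pre-specified minimum.

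Report McNemar's p-value as descriptive only. Both parts are needed, because a margin on the difference in proportions does not by itself measure agreement patient by patient.

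Plus or minus 5 points, borrowed from the sizing contrast, is one candidate margin, but it is an assumption and needs its own justification.

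The cost is a change of wording, plus a statement of the power that 698 gives for the chosen margin and minimum kappa. The equivalence claim becomes harder to meet, and joint power cannot exceed that of the weaker part. If the justified margin is nearer 3 points, or true differences of 2 to 3 points are plausible, 698 pairs fall short. The plan should then say so or revisit the sample size.
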